### Data storage and management

To protect confidentiality, each participant will be assigned a unique study identifier that will be used to link study datasets. Identifying information, including participant name, contact information, and the unique study identifier will be stored in a separate database not to be included in the data analysis. Survey data will be collected and managed using REDCap electronic data capture tools (107, 108) that are hosted on a secure server at the University of Oklahoma Health Sciences Center. Biomarker and body composition data will be manually entered into the REDCap database by research staff. De-identified microbiome sample data will be stored and analyzed at Oklahoma State University Center for Health Sciences. Analytic output files (dietary recall data) will be directed downloaded from the ASA24^®^ website and saved on a secure server at the University of Oklahoma Health Sciences Center. Before analysis, these dietary data will be reviewed for missing nutrient data, portion outliers, and nutrient outliers in accordance with the general guidelines from the National Cancer Institute (NCI) regarding how to review and edit ASA24 data.

### Statistical analysis

We will first examine associations between continuous measures, such as food insecurity on the 10-point scale, DII^®^ scores, CRP level, and various measures of glucose homeostasis, using linear regression. We will compare means using t-tests for categorical variables with 2-levels and ANOVA for variables with 3 or more levels, such as the 4-level food security categorical variable (high, marginal, low, very low food secure).

#### Insulin sensitivity

We will use fasting glucose and insulin measures to calculate the quantitative insulin sensitivity check index (QUICKI) as the primary outcome measure for our analyses where a lower value indicates greater insulin resistance (99). Due to its reliability, reproducibility, accuracy, and positive predictive value across a wide range of co-morbidities, the QUICKI is a widely-accepted surrogate index measure of insulin sensitivity that is recommended for larger, community-based research studies when the laborious, clinic-based hyperinsulinemic-euglycemic clamp technique is not feasible (107). The QUICKI uses the empirically-derived equation QUICKI = 1/[log(I_0_) + log(G_0_)], where I_0_ is fasting insulin (μU/ml), and G_0_ is fasting glucose (mg/dl) (99). The QUICKI has been shown to perform equally to or slightly better than the homeostasis model assessment of insulin resistance (HOMA-IR) across the insulin sensitivity-resistance spectrum (108, 109). Additionally, it offers a slight advantage for measuring changes in insulin sensitivity over time (107, 110), which in consideration of our third aim (examining the effects of a food is medicine intervention on insulin resistance), the QUICKI was selected as the most appropriate outcome measure for the NOURISH-OK study.

#### Dietary intake

We will calculate DII^®^ scores (crude and energy-adjusted) developed by Hebert and colleagues (51) for the full sample with measurement error correction using information from the sub-study. The DII^®^ and the energy-adjusted DII (E-DII™) scores are calculated based on dietary intake of food parameters (i.e., a combination of whole foods and nutrients associated with inflammation). Scores can range from a theoretical low of around -9 to a theoretical high of +8; however, scores are rarely outside the range of -6 to +6. Negative scores represent an anti-inflammatory dietary pattern, while positive scores represent a pro-inflammatory dietary pattern. We hypothesize that DII^®^ score will be positively associated with insulin resistance. We will conduct sensitivity analyses of the relationship between DII^®^ scores and insulin resistance at each level of food security. We hypothesize that DII^®^ scores will be more strongly associated with insulin resistance for food insecure groups than food secure groups (111). These analyses will inform a list of candidate intervention foods for further evaluation in Aim 2. Dietary fiber has been inversely associated with BMI in PLWH (112) and is a source of sustenance for beneficial gut bacteria (113), thus we will also compare the impact of dietary fiber on insulin resistance. We will further explore dietary component factor loadings contributing most strongly to the DII^®^ scores and use discriminant analysis to understand the relationship between DII^®^ score and reported patterns of intake.

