**Methods/design:**

This paper summarizes the protocol for the first aim of the NOURISH-OK study, which involves purposeful cross-sectional sampling of PLWH (n=500) across four levels of food insecurity to test our conceptual framework. Developed in collaboration with community stakeholders, this initial phase involves the collection of anthropometrics, fasting blood samples, non-blood biomarkers, 24-hour food recall to estimate the Dietary Inflammatory Index (DII^®^) score, and survey data. A 1-month, prospective observational sub-study (total n=100; n=25 for each food security group) involves weekly 24-hour food recalls and stool samples to identify temporal associations between food insecurity, diet, and gut microbiome composition. Using structural equation modeling, we will explore how upstream risk factors, including early life events, current discrimination, and community food access, may influence food insecurity and its potential downstream impacts, including diet, other lifestyle risk behaviors, and chronic inflammation, with insulin resistance as the ultimate outcome variable. Findings from these analyses of observational data will inform the subsequent study aims, which involve qualitative exploration of significant pathways, followed by development and testing of a low-DII^®^ food as medicine intervention to reverse insulin resistance among PLWH (ClinicalTrials.gov Identifier: NCT05208671).

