### Study population and eligibility criteria

The target population for the NOURISH-OK study is PLWH who are eligible for Ryan White-funded programs and reside in Oklahoma. An estimated 3,000 PLWH access one or more Ryan White-funded programs annually (49) and represent the study’s known recruitment pool. Nearly half (47%) of these individuals identify as a racial or ethnic minority, including 23.8% Black, 5.8% American Indian, and 10.1% Hispanic (49). An estimated 79.7% are male with most Ryan White clients aged 25-44 (42.7%) and 45-64 years (49.2%) (49). Study eligibility criteria require participants be HIV-positive residents of Oklahoma, financially eligible for Ryan White services (i.e., household income <400% federal poverty level), prescribed antiretroviral therapy (ART) for at least the past 6 months, and ability to provide a 10-hour fasting blood sample. Study exclusion criteria includes receiving treatment for cancer or end-stage renal disease.

A preliminary food needs study among Oklahoma Ryan White clients in 2012 found a high prevalence of very low (47.6%) and low (19.5%) food security in this population (62). To test our theoretical model of food insecurity as a central mediator linking upstream and downstream determinants of insulin resistance, representation at each level of food security status is needed. Therefore, selection criteria will be based on a food security pre-screening using the 10-item US Adult Food Security Survey Measure (63). Enrollment goals are based on food security status to ensure equal representation across four categories of food security: high (n=125), marginal (n=125), low (n=125), and very low (n=125) (**Figure 2**).

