### Prospective observational sub-study procedures

#### Replicate dietary intake and food security recalls

Upon completion of the cross-sectional study, participants will be randomly selected within their food security group for an invitation to participate in a 4-week observational sub-study. Elucidating the influence of food insecurity on dietary intake presents an important methodologic challenge because intake estimates from those with low and/or very low food security may potentially have higher error as compared to those with high or marginal food security. These differences in error may be due to wider fluctuations in food access throughout each month (101) and seasonally (102) for food insecure groups. Therefore, the primary purpose of the sub-study is to collect replicate dietary recalls to obtain a more precise estimate of usual dietary intake for each food security group, in addition to exploring how food security fluctuates from week-to-week. Trained interviewers will collect replicate dietary recalls and food security surveys *via* phone. At sub-study enrollment, subjects will receive a printed guide illustrating standard food units of measure for reference during phone calls to improve reporting accuracy.

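### The hypothesis that DII relates more strongly to insulin resistance in food-insecure groups has no stated test of the difference, and the level-specific error correction is not tied to it

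*Protocol article*

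**What the plan says.** The protocol article, Statistical analysis, Dietary intake, makes a claim about a difference between groups: DII "scores will be more strongly associated with insulin resistance for food insecure groups than food secure groups". The analysis given for it is level by level: "We will conduct sensitivity analyses of the relationship between DII" "scores and insulin resistance at each level of food security". The same section gives the results a use: "These analyses will inform a list of candidate intervention foods for further evaluation in Aim 2".

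The enrolment targets in Study population and eligibility criteria are "high (n=125), marginal (n=125), low (n=125), and very low (n=125". The sub-study that supplies replicate recalls has "n=25 for each food security group" (abstract, Methods/design).

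On recall error, Replicate dietary intake and food security recalls says that "intake estimates from those with low and/or very low food security may potentially have higher error". The article responds in two places. Dietary intake plans an error correction of DII for the full sample from the sub-study. Estimating dietary intake measurement error adds an exploratory sensitivity analysis that would estimate and adjust for error separately at each food security level.

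**The concern.** A stronger association in one group than in another is effect modification. Four associations, each estimated within one level, do not give the size of the difference, its uncertainty or a test of it. A reader left with four separate results is likely to compare which ones are significant, and that comparison varies a great deal by chance when the levels share the same true association.

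Recall error adds a second problem. Random error in a single-day recall flattens the DII slope. If that error is larger in the low and very low groups, their slopes are flattened more. This works against the stated hypothesis, so a true difference could be hidden. One calibration factor applied to everyone would not repair it.

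At stake is whether a stated hypothesis, one of the DII analyses said to inform the Aim 2 food list, gets an answer that can be interpreted.

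**Working it through.** **Inputs from the article.** 125 participants per level, so 250 insecure (low, very low) and 250 secure (high, marginal). Sub-study of 25 per level with four additional recalls, so five per person with the main-study recall. No alpha, correlation, power or error variance is given for this hypothesis.

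**Assumptions.** Two-sided 0.05; true correlations of 0.10 to 0.30; variance ratio VR (error variance over between-person variance) of 1 in the secure groups and 1.5 to 3 in the insecure groups.

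**1. The plan's own figures.** There is no power figure to reproduce. The sums agree: 4 × 125 = 500 and 4 × 25 = 100.

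**2. Is a comparison named anywhere?** The opening of Statistical analysis gives linear regression, t-tests and ANOVA. Dietary intake gives the level-by-level associations. Final structural equation modeling names two modifiers, food utilization skills (on the path from food access to food security) and AIDS diagnosis, and plans invariance testing by AIDS status. There food security is an intermediate variable, not a modifier of the DII path. No DII by food security term or slope contrast appears.

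**3. Separate tests when nothing differs.** Power in one level is approximately p = Φ(atanh(r)·√(n−3) − 1.96), plus a negligible opposite tail. At r = 0.20 and n = 125: 0.2027 × √122 = 2.239, and Φ(0.279) = 0.61. The chance that the four levels do not all agree is 1 − p⁴ − (1−p)⁴ = 1 − 0.138 − 0.023 = 0.84.

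| Common r | Power per level (n = 125) | Four levels disagree | Two pooled groups (250 each) disagree |
|---|---|---|---|
| 0.10 | 0.20 | 58% | 46% |
| 0.15 | 0.39 | 84% | 45% |
| 0.20 | 0.61 | 84% | 20% |
| 0.25 | 0.81 | 58% | 4% |
| 0.30 | 0.93 | 26% | 0.4% |

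**4. Unequal recall error.** With classical error the observed slope is the true slope times λ = 1/(1 + VR). Secure, VR = 1: λ = 0.50. Insecure, VR = 1.5, 2 or 3: λ = 0.40, 0.33 or 0.25. Equal true slopes then appear in the ratio (insecure to secure) 0.80, 0.67 or 0.50. A true slope 1.5 times steeper in the insecure groups appears as 1.5 × 0.80 = 1.20, 1.5 × 0.67 = 1.00 or 1.5 × 0.50 = 0.75. One common calibration factor multiplies both slopes alike and leaves these ratios unchanged.

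**5. Would an interaction test alone be enough?** No. In 4,000 simulated studies with equal true slopes (r = 0.3, 250 per group), a slope-difference test rejected in about 5% when error was equal. With uncorrected VR of 1 versus 2 it rejected in about 14%, and with 1 versus 3 in about 29%, almost always in the direction of secure stronger. The group-specific correction is needed as well.

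**6. What the remedy can deliver.** For 250 versus 250 the SE of a Fisher-z difference is √(2/247) = 0.090. Observed correlations of 0.30 versus 0.10 differ by 0.3095 − 0.1003 = 0.209, and 0.209/0.090 = 2.32 gives 64% power. For 0.30 versus 0.15 it is 42%. The difference detectable with 80% power is (1.96 + 0.84) × 0.090 = 0.25.

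The SE of a reliability of 0.25 from five recalls is √[2(1−0.25)²(1+4×0.25)² / (5×4×(n−1))]. That is 0.097 for n = 25 (95% interval about 0.06 to 0.44) and 0.068 for n = 50 (about 0.12 to 0.38).

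**The case against.** The strongest defence is that the article states no rule of comparing significance across levels. Looking at the relationship in each level is compatible with comparing slopes and confidence intervals, or with level-specific slopes taken from one interaction model, and a fuller analysis plan may name the contrast. The absence of a significance rule is a fact, so the disagreement figures show what could happen if the results were read that way, not what the plan commits to. The defence does not remove the point: for this hypothesis the article does name an analysis, and that analysis does not estimate the difference. For other modifiers the same article names the modification and a formal comparison.

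A reader might infer from the 84% that chance alone would usually produce support for the hypothesis. It would not. The 84% counts disagreement in any direction. At p = 0.61 the chances of 0, 1 or 2 significant results among two levels are 0.152, 0.476 and 0.372. More significant insecure than secure levels therefore occurs with probability (1 − 0.152² − 0.476² − 0.372²)/2 = 0.31. The clean pattern, both insecure and neither secure, has probability 0.61² × 0.39² = 0.06.

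A reader might also infer that the plan expects unequal error and that the DII slopes are therefore distorted. The wording is only that error may be higher. DII is to be corrected, level-specific adjustment is already planned as exploration, and the Discussion returns to the issue. What stands is narrower: the level-specific adjustment is not linked to this contrast, and the correction described under Dietary intake reads as one correction for the full sample.

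Finally, the Introduction (Unpacking the upstream) argues for treating food security as ordinal or continuous rather than as two groups. That is fair, and a two-group contrast should not be the only form.

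**Conclusion.** The point holds in limited form and is of moderate importance. The hypothesis is about a difference in association; the only stated analysis is four within-level associations, which neither estimate nor test that difference. The 58% to 84% disagreement rests on a common correlation of 0.10 to 0.25, 125 per level and two-sided 0.05.

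The measurement-error part is conditional. If error is higher in the insecure groups and one common correction is used, the hypothesised pattern is masked, not created. The ratio of 0.67 rests on assumed variance ratios of 1 and 2. The documents do not show that this will happen.

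The consequence is bounded. The hypothesis is secondary, its analysis is labelled a sensitivity analysis, and the food list draws on the DII analyses without the article saying how this contrast would change it.

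**What to change.** State one model on all 500 participants as the test of this hypothesis: QUICKI on error-corrected DII, food security and their product. Give the slope difference between insecure (low, very low) and secure (high, marginal) with its 95% CI as the result. Because a lower QUICKI means greater resistance, say which sign supports the hypothesis. Add the interaction with the four-level or 10-point measure as support, in keeping with the Introduction, and report the four level-specific slopes as description only.

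Tie the error correction to this model. Estimate it from one mixed model of the sub-study recalls, with within-person variance allowed to differ by food security group, and carry the calibration uncertainty into the CI, for example by bootstrapping both steps together.

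The cost is wording and analysis time; no new data are needed. The limits should be stated: the CI will be wide (about 64% power for observed correlations of 0.30 versus 0.10 and 42% for 0.30 versus 0.15, before calibration uncertainty is added), and group-specific reliability stays imprecise even at 50 versus 50 (SE about 0.07 at 0.25). If a fuller analysis plan already contains this model, one sentence in the protocol pointing to it is enough.

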#### Estimating dietary intake measurement error

For dietary intake estimates, we will conduct an internal regression calibration study using the sub-sample of 100 subjects with four additional dietary recalls to estimate and adjust for measurement error in the remaining sample with single-day recalls (114). We will use the methods of triads to combine dietary recall data with dermal carotenoid scores to more precisely estimate true carotenoid and total fruit and vegetable intake (115, 116). Since chronic inflammation and smoking are both independently associated with lower beta-carotene concentrations (116), we will control for these confounders, if needed. Additionally, we will explore whether measurement error varies by food security status using sensitivity analysis to estimate and adjust for measurement error at each food security level. We will estimate variance in SAS using the Restricted Maximum Likelihood Estimation method and variance ratios as the error variance/variance across individuals. The within- (CVw=Sw/mean of each nutrient) and between-individual (CVb = Sb/mean of each nutrient) coefficient of variation (CV) will be estimated using Beaton’s formula (117). The CVw will then be used to estimate the number of 24-hr food recall days needed to estimate accurate dietary intakes among PLWH, and whether the number of recall days differ by food security status (117). Findings will be applied to modify the number of dietary recalls collected to evaluate the impact of the NOURISH-OK intervention (Aim 3).

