#### Blood sampling, processing, and analysis

Before blood samples are collected, research staff will confirm each participant has fasted a minimum of 10 hours by asking the last time the participant ate or drank anything besides water. Venous blood samples will be collected by a trained phlebotomist using one BD Vacutainer serum tube, one BD Vacutainer EDTA plasma tube, one BD Vacutainer Heparin tube, one BD Vacutainer P800 plasma tube, and one BD Vacutainer CPT tube for peripheral blood mononuclear cells (PBMC). Samples will be transported to the designated study lab and processed within 2 hours of draw according to manufacturer’s instructions. Plasma and serum aliquots will be stored at −80°C until analysis. Peripheral blood mononuclear cells aliquots will be stored for less than 75 hours at −80°C and then transferred to liquid nitrogen vapor phase for cryopreservation until analysis. Laboratory measures, including serum insulin, blood glucose, c-reactive protein, hemoglobin A1c, and blood cotinine, are summarized in **Table 2**.

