#### Nutrition and vital signs assessment

Trained research assistants will then conduct a nutrition assessment including height, weight, waist circumference, wrist circumference, grip strength, and a segmental bioelectrical impedance analysis test. Additional vital signs will include resting heart rate, blood oxygen level, and blood pressure. Resting heart rate, waist circumference, gender, and age will be used to estimate cardiorespiratory fitness (84, 86). We will collect one 24-hr food recall using the Automated Self-Administered 24-hour (ASA24^®^) Dietary Assessment Tool as our primary measure of dietary intake from all subjects (91). We will additionally measure skin carotenoid concentration using Reflections Spectroscopy (RS) (83). This will serve as a concentration biomarker to adjust for measurement error in estimated carotenoid and total fruit and vegetable intake from the ASA24^®^-generated dietary intake estimates.

We will measure height and weight (without shoes) to calculate body mass index (BMI) using a medical grade stadiometer and scale. We will measure central adiposity using waist circumference adapted from NHANES guidelines (96). To minimize participant discomfort, participants will identify body landmarks for self-measure in front of a mirror with assistance from staff. We will conduct segmental bioelectrical impedance analysis (BIA) using the Quantum V Segmental BIA (RJL Systems). Participants who may be pregnant or who have implanted electronic devices will be excluded from this measure. Participants with metal surgical implants present on one side of the body will complete a one-sided measure using the side of the body without the implant. Segmental body fat readings (right arm, left arm, right leg, left leg, and torso) will be used to further identify body type pattern associated with insulin resistance (97). We will minimize BIA measurement error associated with dehydration by providing 16 oz. of water 30 minutes prior to measurement. Collectively, these measures will be used to estimate nutritional and functional status.

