	** *Weekly Measures (4 timepoints)* **
**Dietary intake**	**Dietary quantity:** Absolute and energy-adjusted estimates of energy, macro- and micronutrients, caffeine, and alcohol (Single day 24-hour food recall using ASA24^®^) **Dietary quality:** Inflammatory potential of overall diet (DII^®^/E-DII^®^ using ASA24^®^data)
**Food security**	**Food security in the 30 days:** 10-item USDA Adult Food Security Survey Module (Timepoint 1) (63) **Food security in the past week:** Adapted from previous study to assess daily food security (105) that includes modified HH2, HH4, AD2 measures from 10-item USDA Adult Food Security Survey Module (Timepoints 2 – 4) (63)
**Sleep quantity**	**Sleep quantity:** 1-item measure of sleep duration in the past 24-hours (adapted from 2007 NHANES National Center for Health Statistics Sleep Disorders survey) (11)
**Physical activity**	**Physical activity:** 2-item measure of aerobic activity in the past 24-hours adapted from (84) **Sedentary behavior:** 1-item measure to estimate sedentary behavior minutes in the past 24-hours (adapted from the International Sedentary Assessment Tool) (85)
**Intestinal transit time**	**Self-reported stool sample consistency**: Bristol stool chart (106) **Date and time of most recent bowel movement** at time of dietary food recall (self-report)
**Gut microbiome**	**Self-sampling stool test** (OMNIgene•Gut, OMR-200.100; DNA Genotek) **Diversity indices:** Alpha (e.g., Shannon, Faith’s phylogenetic diversity) and beta diversity analyses **Relative abundance** of specific bacterial groups (e.g., Firmicutes, Bacteroidetes, Proteobacteria, Bacteroides, Prevotella, etc.) **Differential abundance analyses** using participant and dietary metadata
**Medication changes**	Changes in microbiome-altering prescribed and over-the-counter medications reported during Aim 1 enrollment and sub-study participation period

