In addition to elucidating the various potential mechanisms by which food insecurity shapes health risks, the NOURISH-OK study will support validation of dietary assessment measures in PLWH. These measures include dermal carotenoids as a biomarker for total carotenoid and total fruit/vegetable intake and construct validity of the DII^®^ as a predictor of inflammation in PLWH. Because carotenoids, fruits, and vegetables correlate with other nutrients that comprise the DII^®^ score and inflammatory markers, dermal carotenoids may be a useful non-invasive alternative to intensive dietary collection methods in future PLWH studies, including measures of intake and dietary intervention adherence. Although tested extensively in diverse populations (129, 130), this surrogate biomarker has not been studied among PLWH. The NOURISH-OK sub-study will further address methodologic gaps by exploring whether there are differences in dietary intake measurement error based on food insecurity status. If food security status is found to be related to measurement error, it will be paramount that future research investigating the role of food insecurity on dietary intake incorporate methods to adjust for this error. Furthermore, the sub-study’s oral and gut microbiome analyses will answer important questions about whether food insecurity is associated with distinct microbiome profiles and whether these profiles are attributable to diet and insulin resistance among PLWH. Finally, the NOURISH-OK study addresses additional methodologic gaps in health behavior research by including additional validation studies of other lifestyle behaviors among PLWH beyond diet, including self-reported tobacco (validated with serum cotinine) and perceived stress (validated with CRP).

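### The method of triads has only two kinds of measure to work with, so any error shared by repeat recalls overstates recall validity and understates skin-carotenoid validity

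*Protocol article*

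**What the plan says.** Under Estimating dietary intake measurement error, the article plans two things. The first is regression calibration in a "sub-sample of 100 subjects with four additional dietary recalls to estimate and adjust for measurement error" in the remaining participants, who have one recall each. The second is the triad, applied to carotenoids and to fruit and vegetables overall: "We will use the methods of triads to combine dietary recall data with dermal carotenoid scores to more precisely estimate true carotenoid". The next sentence begins "Since chronic inflammation and smoking are both independently associated with lower beta-carotene concentrations" and promises control for both factors, but only where it proves necessary.

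The section Nutrition and vital signs assessment gives skin carotenoid its role: "This will serve as a concentration biomarker to adjust for measurement error in estimated carotenoid and total fruit and vegetable intake". The Discussion proposes it as a possible non-invasive alternative to intensive dietary collection in future studies of people living with HIV, and notes that "this surrogate biomarker has not been studied among PLWH".

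The instruments are listed in full. The replicate measure in Table 3 is a "Single day 24-hour food recall using ASA24", the same tool as in the main study. By mode, "Trained interviewers will collect replicate dietary recalls and food security surveys" by phone. The section on blood sampling reads "Laboratory measures, including serum insulin, blood glucose, c-reactive protein, hemoglobin A1c, and blood cotinine"; no carotenoid assay is among them. Tables 2 and 3 contain no food frequency questionnaire and no food record.

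**The concern.** The method of triads infers each measure's correlation with unobserved true intake from the three pairwise correlations. It is valid only if the three errors are independent of one another. Here two arms must be the same self-report method. A person who habitually over- or under-reports fruit and vegetables does so in the visit recall and in the replicates. Averaging replicates removes day-to-day variation but not that stable component, and the triad reads the shared error as shared truth.

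At stake is the validation result. The article wants to know how good skin carotenoid is relative to recalls. A triad built this way favours the recall whenever s is above zero.

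A second and separate issue is that skin carotenoid is lowered by inflammation and smoking, while CRP is the study's inflammation measure and a mediator in its conceptual model. Intake corrected with this marker may be associated with CRP for reasons unrelated to diet.

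**Working it through.** **Inputs from the article.** Two kinds of measure; 100 participants with four replicate recalls; skin carotenoid as the only carotenoid marker. It states no validity coefficient or error variance, so there is no figure to reproduce.

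**Assumed inputs.** True intake variance 1; shared reporting error variance s = 0, 0.25, 0.5, 1.0; day-to-day variance w = 2; true skin-carotenoid validity 0.5, with its error independent of recall error.

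**Model.** Q = single recall, variance 1+s+w. R = mean of four replicates, variance 1+s+w/4. M = skin carotenoid. Then

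- r(Q,R) = (1+s) / sqrt[(1+s+w)(1+s+w/4)]
- r(Q,M) = 0.5 / sqrt(1+s+w)
- r(R,M) = 0.5 / sqrt(1+s+w/4)

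**Triad formulas.**

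- Recall: sqrt[r(Q,R) r(Q,M) / r(R,M)] = sqrt[(1+s)/(1+s+w)], which is the true value 1/sqrt(1+s+w) times sqrt(1+s).
- Skin carotenoid: sqrt[r(Q,M) r(R,M) / r(Q,R)] = 0.5 / sqrt(1+s).

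The marker cancels out of the recall coefficient, which is simply the square root of the single recall's repeatability.

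**Numbers at s = 0.5, w = 2.** Variances 3.5 and 2.0; r(Q,R) = 1.5/sqrt(7) = 0.567; r(Q,M) = 0.267; r(R,M) = 0.354. Recall: sqrt(0.567 × 0.267 / 0.354) = 0.655, true 1/sqrt(3.5) = 0.535. Skin carotenoid: sqrt(0.267 × 0.354 / 0.567) = 0.408, true 0.500.

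| s | Factor sqrt(1+s) | Single recall, true → triad | Mean of four, true → triad | Skin carotenoid, true → triad |
|---|---|---|---|---|
| 0 | 1.00 | 0.577 → 0.577 | 0.816 → 0.816 | 0.500 → 0.500 |
| 0.25 | 1.12 | 0.555 → 0.620 | 0.756 → 0.845 | 0.500 → 0.447 |
| 0.5 | 1.22 | 0.535 → 0.655 | 0.707 → 0.866 | 0.500 → 0.408 |
| 1.0 | 1.41 | 0.500 → 0.707 | 0.632 → 0.894 | 0.500 → 0.354 |

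The factor does not depend on w (at w = 3 and s = 0.5, single recall goes from 0.471 to 0.577). The ratio of recall to skin-carotenoid validity is inflated by 1+s. At s = 1.0 the single recall and the marker are equally valid (0.500 each), yet the triad shows 0.707 against 0.354.

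**Stability.** In 4,000 simulated samples of 100 with s = 0.5 and w = 2, about 20% gave an inadmissible coefficient for the mean-recall arm (above 1 or undefined).

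**CRP and smoking.** Give the marker an assumed dependence of 0.2 or 0.4 on a standardised CRP/smoking factor unrelated to true intake, and predict intake from recall plus marker (400,000 simulated persons). Left unadjusted, predicted intake correlates with the factor at −0.12 or −0.21; with the marker adjusted, 0.00. If true intake and the factor do correlate, at −0.3, adjustment lowers the marker's correlation with true intake from 0.53–0.55 to 0.46. In every scenario the triad's recall coefficients stayed at 0.655 and 0.866.

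**The case against.** The strongest reply is that this is a secondary validation analysis, that the size of s is unknown, and that a protocol article may leave the details to an analysis plan. The replicates are taken by interviewers, while the ASA24 is by name self-administered, so part of the reporting error may differ between arms. If errors are independent, the triad is exact. This stands: the bias is conditional and its size rests on assumptions. It does not remove the point, because the article names both the method and all the instruments, and no analysis plan can supply a third kind of measure that is not collected. A change of mode may lower s; it does not make two self-reports by one person independent.

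A reader might infer more than the documents support:

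- **That the DII–CRP–QUICKI path is contaminated.** The triad covers carotenoid and fruit and vegetable intake only. The DII is to be corrected with sub-study information, and the article describes that as regression calibration on replicate recalls. Nothing says biomarker-corrected intake enters these models.
- **That dependence on CRP and smoking also distorts recall validity.** It cancels.
- **That adjustment cannot help.** It removes the spurious link when intake and CRP are unrelated; when they are related, it costs signal.
- **That 400 of 500 participants lacking a third measure defeats the method, or that using each measure to assess the other is circular.** Triad coefficients are group-level, can be estimated in the 100, and are estimated jointly by design.

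Nor is the recall–biomarker correlation corrected for within-person variation an escape. It equals [0.5/sqrt(1+s+w/4)] / sqrt[(1+s)/(1+s+w/4)] = 0.5/sqrt(1+s), which is the triad's own skin-carotenoid coefficient.

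**Conclusion.** The point holds in conditional form. With only recall and skin carotenoid available, the triad overstates recall validity by sqrt(1+s) and understates skin-carotenoid validity by the same factor, for any s above zero. Over the assumed range of 0 to 1.0 the factor is 1.00 to 1.41. The direction follows from the design; the size does not, since the article gives no error variances.

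The lower-bound reading of the skin-carotenoid coefficient also needs the marker's error to be unrelated to reporting error. When the CRP/smoking factor was allowed to correlate with reporting error, the gap changed and in one case nearly closed (0.443 against a true 0.464, at s = 0.5, dependence 0.4, correlation −0.3). This is one more reason to settle the smoking and CRP rule in advance.

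A spurious association of biomarker-corrected intake with CRP is a risk left open by the conditional wording, not an established result. The primary outcome is untouched. The change should still be made, because it alters what the validation can conclude.

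**What to change.** 1. State that the triad arms are the single main-study recall, the sub-study replicate recalls and skin carotenoid, and state the independence assumption.
2. Report the recall coefficient as an upper bound and the skin-carotenoid coefficient as a lower bound. Label any de-attenuated recall–biomarker correlation a lower bound too. Add a sensitivity analysis over s, for example 0, 0.25, 0.5 and 1.0, and do not present triad output as an unbiased estimate of true intake.
3. Replace the conditional wording on inflammation and smoking with a fixed rule for how cotinine and CRP enter the validation analysis.
4. In any model with CRP or QUICKI as outcome, use intake calibrated from recalls alone, not intake corrected with skin carotenoid.

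The cost is analysis-plan wording and a short sensitivity table; no new data are needed. Fruit and vegetable intake will be somewhat less precise without the marker, and recall-only calibration still retains the shared reporting error, which should be stated as a limitation.
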